### Study endpoints and data collection

Study outcomes, tools, and time points for measurement are outlined in Table 3. Follow-up will occur approximately 6 months post-enrollment (allowed range 140–224 days after baseline interview), according to outpatient hepatology scheduling availability. If a follow-up appointment is missed, a second appointment will be offered to the patient within the allowed time frame. If the second appointment is missed, the patient will be considered lost to follow-up for *t*
_3_ survey endpoints.

**Table 3 Tab3:** Outcomes and other measures of the medication management and education intervention

Categories/variables	Measure	Collection week
Medication discrepancies		
Between drug name and dosage Frequency of per-patient discrepancies Severity of discrepancies	Patient interview Questionnaire Medical record review	*t* _0,_ *t* _3_
Medication-related problems (intervention arm only)		
Adverse drug reaction Drug interaction Untreated, undertreated, or overtreated indication Other medication-related barriers	Patient interview Questionnaire	*t* _0,_ *t* _3_
Adherence		
Self-reported medication adherence Affordability	MMAS-8 Patient interview	*t* _0,_ *t* _3_
Quality of life		
Health-related quality of life Abdominal and systemic symptoms Emotional functioning, fatigue, and worry Daily activity	CLDQ Brief IPQ	*t* _0,_ *t* _3_
Beliefs and perceptions		
General medication beliefs Beliefs about liver disease medications Illness perceptions	BMQ-General BMQ-Specific Brief IPQ	*t* _0,_ *t* _3_
Knowledge/health literacy		
Knowledge of causation Dietary modification including sodium restriction Self-monitoring requirements Safe analgesia Source of medication-related information	Questionnaire Brief IPQ	*t* _0,_ *t* _3_
Hospitalization		
Liver-related hospitalization Non-liver-related hospitalization Duration of stay	Medical record review	*t* _3,_ *t* _4_ (and 3 years)
Survival		
Liver-related mortality Non-liver-related mortality	Medical record review	*t* _3,_ *t* _4_ (and 3 years)
Cost		
Cost of service implementation Potential cost savings	Cost modeling	After study completion

*Abbreviations: BMQ* Beliefs about Medicines Questionnaire, *Brief IPQ* Brief Illness Perception Questionnaire, *CLDQ* Chronic Liver Disease Questionnaire, *MMAS-8* Eight-question Morisky Medication Adherence Scale

### Primary outcome

#### Medication discrepancies

Discrepancies between patient-reported and clinician-documented current medications will be obtained via the patient questionnaire (medication recall), patient interview (reconciliation for intervention participants only), and medical record review (clinician documentation). The clinical significance of discrepancies will be determined by blinded comparison at the completion of the study using a risk matrix tool (Fig. 2), which assigns a composite ranking of severity, likelihood, and duration, as described in the Methods subsection “Medication-related problems” above. Discrepancies (between medications, doses, and frequency of administration) will be examined at baseline and follow-up (*t*
_3_) for both groups. A composite endpoint of frequency (counts of) and potential risk will be examined by measuring total frequency of high/very high risk discrepancy occurrence and the frequency of high/very high risk discrepancy occurrence per patient.

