## Methods/design

### Study aims and hypotheses

The primary aim of the study is to determine whether the intervention (medication review, reconciliation, and additional education by a clinical pharmacist) reduces the frequency (counts) and severity (measure of clinical significance) of discrepancies between patient-reported and medical record-documented “current” medications. The secondary aims are to describe the impact of the intervention on medication adherence, quality of life (QoL), medication and illness beliefs, patient knowledge of disease and self-management tasks related to decompensation history and prescribed therapy, and the frequency of hospitalization for management of cirrhosis-related complications, non-cirrhosis-related complications, and survival. The sustainability of the intervention in the current health care system in relation to costs and cost-effectiveness will also be evaluated.

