**Fig. 1 Fig1:**
[figure not shown]
Standard Protocol Items: Recommendations for Interventional Trials (SPIRIT) flow diagram of participant recruitment and study navigation. *MRP* Medication-related problem

All participants will complete a baseline survey prior to their scheduled outpatient clinic review. Validated questionnaire tools will be used to determine baseline medication adherence, medication beliefs, illness perceptions, and QoL, in addition to patient knowledge of important dietary and lifestyle modifications. The survey will be completed with a study coordinator over the telephone or in person in a private clinic room, or it will be self-completed by the participant in the clinic waiting room. Patient carers or family members will be involved if necessary.

Usual care participants will subsequently receive routine review and education by their hepatologist according to the current model of care in the hepatology clinic. Intervention participants will be reviewed by a clinical pharmacist to receive the education and medication management intervention (described below) in addition to routine review and education by their hepatologist. Intervention participants will also receive three further educational contacts from the clinical pharmacist in addition to scheduled routine hepatologist review within the following 6-month period.

All participants will be resurveyed at follow-up (*t*
_3_, approximately 6 months post-enrollment) to explore changes in their medication adherence, medication beliefs, illness perceptions, QoL, and knowledge. Patient outcome data will be collected at 52 weeks (*see* “Study endpoints and data collection” section below).

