### Intervention description

During the initial encounter with each intervention patient (and carer/family member if present), the clinical pharmacist will obtain a complete, reconciled list of current medications and identify MRPs. The pharmacist will use open and closed questions to ascertain adherence, other medication-taking behaviors, and medication needs on an individualized basis. Participating patients will receive medication- and lifestyle-related education and advice tailored to their needs (decompensation history and medications) and receptiveness (Table 2). The pharmacist will also collaborate with the patient’s general practitioner and hepatologist to optimize therapy, facilitate resolution of MRPs, and monitor issues where required.

Subsequent contact with participants will be made at 4–6 weeks (*t*
_1_) and 12–14 weeks (*t*
_2_) after the baseline interview to discuss changes in prescribed therapy; identify new MRPs and previously identified MRPs that are ongoing; reiterate advice provided at baseline; and provide additional relevant education about medications, lifestyle modifications, and self-management of cirrhosis to build on previous discussions. Promotion of a patient-clinician partnership will be central to each discussion to encourage functional health literacy and self-efficacy with regard to patient confidence to raise questions and discuss issues with health care providers.

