### Medication reconciliation

Using information from several sources (including the patient, general practitioner, pharmacy, own medications, carer), the clinical pharmacist will construct a reconciled list of current pharmacotherapy. The reconciled list of medications will be made available to other clinicians in the patient’s medical record, and a patient-friendly guide will be constructed using the approved statewide template. This guide will be printed and provided to the patient. The patient will be encouraged to take it to all health care appointments and use it at home to aid with compliance and memory. The guide will also contain additional medication management and lifestyle points related to prescribed therapy, such as low-salt diet reminders for patients who are prescribed diuretics in the management of ascites. Patients will be encouraged to manually edit the medication guide when therapy is altered.

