#### Medication-related problems

Intervention participants may have MRPs identified during their interview that warrant follow-up action or monitoring. The pharmacist will document the types of MRPs identified, the action or monitoring required, and the steps taken toward resolution in patients’ medical records and using the structured data collection tool. This information will not be available for usual care participants, because they will not have a medication review. The change in frequency (count) and potential harm (risk matrix) of MRPs will be assessed using an equivalent time sample where the intervention group is its own control. The clinical significance of MRPs will be determined by blinded comparison at the completion of the study using a risk matrix tool (Fig. 2), as described in the Methods subsection “Medication-related problems” above.

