Differences in the study endpoints of interest will be examined between the intervention and control groups at baseline and at follow-up. The endpoints will be examined at baseline to test for homogeneity between groups (effectiveness of randomization) and to identify clinical variables that may influence endpoints (e.g., Model for End-Stage Liver Disease score; Child-Turcotte-Pugh classification; decompensation history, including event date, type, severity, and recurrence; hospitalization frequency; age; sex; biochemical abnormalities; and other prognostic variables). Clinically significant differences at baseline between groups will be adjusted for during the final analysis. Changes in the frequency of medication discrepancies, self-reported adherence, QoL, medication beliefs, illness perceptions, and patient knowledge at follow-up will be examined to measure the effect of the intervention on study outcomes at group and individual levels. The primary endpoint of medication discrepancies will be explored using total frequency of instances and frequency of instances per patient and per medication group. Comparison between intervention and control groups at baseline and *t*
_3_ will be made using total number of instances per group, total number of high/very high risk instances per group, mean/median number of instances per patient, and mean/median number of high/very high risk instances per patient.

Predictors of clinical outcomes will be identified using binary logistic regression to determine the OR (95% CI). A multivariable logistic regression model will be used to determine independent predictors for patient outcomes. The multivariable logistic regression model will be constructed using variables of clinical significance (severity of disease; decompensation history, including date, type, severity, and frequency of events; other prognostic variables) and statistical significance as determined by univariate analysis.

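### The primary discrepancy count has an extra source, pharmacist reconciliation, in the intervention arm only, and the between-arm comparison is not limited to shared sources

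*Protocol article*

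**What the plan says.** The aim, in Study aims and hypotheses, concerns "discrepancies between patient-reported and medical record-documented “current” medications". That comparison has two sides, and both exist in each arm.

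The Primary outcome section then names three sources: "patient questionnaire (medication recall), patient interview (reconciliation for intervention participants only), and medical record review (clinician documentation". The middle one is marked as specific to one arm. The same paragraph continues: "Discrepancies (between medications, doses, and frequency of administration) will be examined at baseline and follow-up", for both groups.

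Table 3 lists patient interview, questionnaire and medical record review as the measures for discrepancies at t0 and t3. It sets no arm limit on that row, although the next row (medication-related problems) is labelled as intervention arm only.

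The Data analysis section compares the arms on "total number of instances per group, total number of high/very high risk instances per group, mean/median number of instances per patient", and on the per-patient high/very high risk count. It does not say which sources feed these counts.

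Usual care has no counterpart to the reconciliation. In the secondary-outcome section on medication-related problems, the protocol says of those data: "This information will not be available for usual care participants, because they will not have a medication review". The Medication reconciliation section describes a list built from the patient, general practitioner, pharmacy, own medications and carer, and adds: "The reconciled list of medications will be made available to other clinicians", in the patient's medical record.

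The blinded comparison in the Primary outcome section covers the clinical significance of discrepancies. No masking is stated for the step that finds and counts them.

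**The concern.** A randomised comparison of counts needs the same counting procedure in both arms. Here one arm has an additional, structured look at the medication list, drawing on several informants, and the plan treats that look as a source of the outcome. Whatever it adds to or removes from the count appears in one arm only and will be read as treatment effect. Randomisation does not balance it, because it arises after allocation.

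If interview-derived findings enter the t0 count, the planned baseline comparison is affected in the same way. The sample size rests on the per-patient count (3.12 to 1.56), so the step with no stated masking produces the very quantity on which the trial is powered.

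**Working it through.** **Inputs.** From Power calculation and sample size determination: control mean 3.12, SD 2.5, intervention mean 1.56, 41 per arm, power at least 80%. From Data analysis: two-sided α = 0.05, one-way analysis of variance for normally distributed outcomes (with two groups, equivalent to the t-test). Assumed: 1:1 allocation and SD 2.5 in both arms.

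**Reproducing the plan's figure.** Difference = 3.12 − 1.56 = 1.56.

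n per arm = 2 × [2.5 × (1.960 + 0.842) / 1.56]² = 40.3, rounded up to 41. The stated figure is reproduced. Power at 41 per arm is 80.7% by the normal approximation and 79.7% by the t-test. The t-test is used below.

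**Standard error and noncentrality.** SE = 2.5 × √(2/41) = 0.552. Noncentrality = observed difference / 0.552, on 80 degrees of freedom.

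**Case 1: the planned effect is real and the interview adds discrepancies in the intervention arm.** The additions are assumptions; the documents give no figure.

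| Added per intervention patient | Observed difference | Noncentrality | Power |
|---|---|---|---|
| 0 | 1.56 | 2.83 | 79.7% |
| 0.5 | 1.56 − 0.5 = 1.06 | 1.92 | 47.5% |
| 1.0 | 1.56 − 1.0 = 0.56 | 1.01 | 17.1% |

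**Case 2: the planned effect is real and the interview clears apparent discrepancies.** If it clears 0.5 per patient, the observed difference is 1.56 + 0.5 = 2.06. The apparent reduction is then 2.06/3.12 = 66% when the true one is 50%.

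**Case 3: no true effect, both means 3.12.** A net ascertainment shift, in either direction, gives these two-sided rejection probabilities:

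| Assumed shift | Spurious difference | Rejection probability |
|---|---|---|
| 0% | 0 | 5% |
| 10% | 0.31 | about 9% |
| 20% | 0.62 | about 20% |
| 30% | 0.94 | about 39% |

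If the shift lowers the intervention count, nearly all of these rejections would be reported as benefit.

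**The case against.** **Both arms may be interviewed.** The abstract says that current medications come from survey, interview and records without separating the arms, and the follow-up window is counted from a baseline interview for participants generally. The bracket in the Primary outcome section could then mean that only the reconciliation is arm-specific, which would bring Table 3 into line. This is a fair reading and makes the asymmetry smaller. It does not remove it, because one arm still has an ascertainment step that the other lacks.

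**The aim already implies a common count.** It needs only patient report and medical record, and all participants complete the baseline survey before clinic review. This stands, and it makes the problem repairable. But the Primary outcome and Data analysis sections do not restrict the comparison to that count.

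**The filed reconciled list is part of the treatment.** The aim defines the intervention as review, reconciliation and education, so better documentation is one legitimate way to reduce mismatch. This stands. A correction must not strip the list out of the comparator, as that would remove part of the effect under study.

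**Stronger readings that the documents do not support.**
- A reader might infer that the intervention count is necessarily inflated. The documents do not fix the direction.
- A reader might infer that the damage cannot be undone. A count from shared sources undoes it, provided that the source of each discrepancy can be told apart.
- A reader might extend the point to adherence, which is examined by MMAS-8 and interview. The MMAS-8 score comes from a questionnaire given to both arms, and nothing says that the interview alters it.
- A reader might tie in the contact schedule: "Intervention participants will also receive three further educational contacts from the clinical pharmacist", yet Intervention description times only two, beginning "Subsequent contact with participants will be made at 4–6 weeks" and then at 12–14 weeks. These sections should be reconciled, but this is a separate point. That the third contact coincides with outcome capture at t3 is conjecture, and the flow figure is not available here.

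**Conclusion.** The concern holds in this form: the protocol makes reconciliation a source of the primary outcome in one arm, compares counts between arms without limiting them to shared sources, and states masking only for the risk rating. Carried out as written, the primary comparison can be biased, in a direction that the documents do not determine.

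The size is unknown. The shifts of 0.5 and 1.0 per patient and of 10% to 30% are illustrations with SD held at 2.5, not estimates. They show that a modest shift matters at 41 per arm: half a discrepancy per patient costs roughly 32 percentage points of power (79.7 − 47.5), and a 20% shift under the null roughly quadruples the false-positive rate. The defect lies in the counting rule, so it can be repaired, but it should be settled before the primary outcome is counted.

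**What to change.** 1. In Primary outcome, Data analysis and Table 3, define the primary count in both arms, at t0 and t3, as questionnaire medication recall against clinician-documented current medications in the medical record. This matches the stated aim.
2. Keep whatever the record contains as the comparator, including the filed reconciled list, because improved documentation is part of the intervention effect.
3. Have discrepancies listed and counted from de-identified, arm-masked extracts, extending the de-identification and random ordering already planned for the clinician panel. Masking will be incomplete where the record content reveals the arm; say so.
4. Report discrepancies found only through the interview separately, as descriptive data for the intervention arm.
5. For participants who have not yet reached t3, capture the questionnaire before any pharmacist contact at that visit.

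**Cost.** Steps 1 to 4 need changed wording and a defined extraction procedure, and no new data. Some discrepancies known to the pharmacist will be left out of the primary count. The Trial status section says that recruitment is complete, so step 5 may come too late for some participants; the counting rule and masked listing can still be applied to all.

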#### Hypotheses

Compared with patients receiving usual care, patients who receive the tailored (additional) education and medication management intervention are hypothesized to benefit in the following ways:

(H1) Fewer medication discrepancies

(H2) Improved medication adherence

(H3) Improved QoL

(H4) Improved illness perceptions

(H5) Improved medication beliefs

(H6) Improved knowledge of disease self-management tasks related to prescribed medications

(H7) Fewer hospital admissions

(H8) Longer survival time

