### Medication-related problems

During patient interviews, the clinical pharmacist will identify actual and potential MRPs and document these in the patients’ medical notes and on a structured data collection form. The pharmacist will then facilitate the resolution or monitoring of individual MRPs with other relevant clinicians as appropriate and document each outcome in patients’ medical notes and data collection forms.

The clinical significance of MRPs (and medication discrepancies) will be assessed by a clinician panel using a risk matrix (Fig. 2) modified from the Metro North Health Service Risk Management Framework [19]. The matrix assigns a composite risk of prospective severity and likelihood of potential harm, as well as duration of time until potential harm may occur, as a consequence of the MRP. The panel of clinicians will comprise at least one clinical pharmacist, hepatologist, and general physician/pharmacologist who have experience in managing patients with cirrhosis. MRPs will be de-identified, randomized, and independently assessed by at least two members of the panel. Relevant clinical information will accompany the de-identified MRPs, but not details of patient outcomes or MRP resolution, to ensure unbiased prospective assessment of potential harm. Consensus of individual rankings will be used to determine the final measure of potential harm. Where there is disagreement between individual rankings, a roundtable panel discussion will be called to facilitate consensus.

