### Power calculation and sample size determination

On the basis of a primary endpoint of a 50% reduction in medication discrepancies (3.12 ± 2.5 per patient [6] to 1.56 per patient), 41 participants will be required per treatment arm to achieve ≥80% statistical power. Median survival in decompensated cirrhosis is 2 years [37]. Therefore, a 6-month mortality rate between 10% and 15% among the study cohort is predicted. The Hepatology Outpatient Centre’s attendance failure/reschedule rate is approximately 20%. Therefore, a possible 30% loss will be accounted for, and at least 106 participants will be recruited.

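### Blinding is stated for the risk ranking of discrepancies but not for finding and counting them, and one source for the count exists in the intervention arm only

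*Protocol article*

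**What the plan says.** The primary outcome section of the protocol article (Medication discrepancies) has two steps.

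- **Finding the discrepancies.** "Discrepancies between patient-reported and clinician-documented current medications will be obtained via the patient questionnaire (medication recall), patient interview" and medical record review. The interview carries the qualifier "reconciliation for intervention participants only". The article does not name the person who compares the two lists, and does not say whether that person is masked.
- **Ranking them.** "The clinical significance of discrepancies will be determined by blinded comparison at the completion of the study", using the risk matrix. The Medication-related problems section, which covers discrepancies as well, gives the mechanism: "MRPs will be de-identified, randomized, and independently assessed by at least two members of the panel".

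Under Medication reconciliation, "the clinical pharmacist will construct a reconciled list of current pharmacotherapy" from several sources, and that list is placed in the patient's medical record. Intervention description shows that this pharmacist is the one who delivers the intervention.

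The unranked count carries much of the primary analysis. The list of hypotheses opens with "H1) Fewer medication discrepancies", without any limit by risk. The sample size is set "On the basis of a primary endpoint of a 50% reduction in medication discrepancies", from 3.12 to 1.56 per patient. Data analysis plans four between-arm comparisons. Two use all instances (per group and per patient) and two use only those ranked high or very high risk.

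**The concern.** A discrepancy enters the data only when someone sets the patient's list against the record and decides that a difference in drug, dose or frequency counts. A blind that begins after this decision cannot restore items that were never listed in one arm, or remove items that were listed too readily.

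Two features stated in the article make this step depend on the arm. First, an extra interview, held by the person delivering the intervention, feeds the count in one arm only. Second, the record used as one side of the comparison holds the pharmacist's list in that arm, so a reader of the record can infer the allocation.

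The direction is open. An extra source could uncover more discrepancies in the intervention arm and hide a benefit. A counter who has inferred the arm could list fewer there and create a benefit. Either would bias the result on which the first hypothesis is judged.

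**Working it through.** **1. Which quantity the sample size uses.** Inputs from Power calculation and sample size determination: means 3.12 and 1.56 (difference 1.56), SD 2.5, power at least 80%. From Data analysis: two-sided 5%.

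n per arm = 2 × (1.960 + 0.842)² × 2.5² / 1.56² = 2 × 7.85 × 6.25 / 2.434 = 40.3, rounded up to 41.

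This reproduces the stated 41 per arm. The inputs are counts of all discrepancies with no restriction by risk, so the sample size rests on the step for which no blinding is stated.

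**2. How large a difference reaches significance.** The standard error of the difference at 41 per arm is 2.5 × √(2/41) = 0.552. With 80 degrees of freedom the critical t is 1.99, so an observed difference of about 1.10 per patient gives p < 0.05.

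**3. What an ascertainment shift would do.** The article gives no size for such a shift, so every value below is an assumption shown as a range. The calculation is a two-sample t test with the noncentral t distribution and noncentrality = difference / 0.552. The fourth column has no true effect. The last column has a true reduction of 1.56 and a shift working against it, so the difference is 1.56 minus the shift.

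| Assumed shift per patient | As % of 3.12 | Noncentrality, no true effect | Two-sided rejection, no true effect | Power if the shift opposes a true 1.56 |
|---|---|---|---|---|
| 0 | 0 | 0 | 5.0% | 79.7% |
| 0.25 | 8.0 | 0.45 | 7.3% | 65.0% |
| 0.31 | 9.9 | 0.56 | 8.6% | 60.9% |
| 0.50 | 16.0 | 0.91 | 14.6% | 47.5% |
| 0.62 | 19.9 | 1.12 | 19.9% | 39.1% |
| 1.00 | 32.1 | 1.81 | 43.2% | 17.1% |

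The 79.7% in the first row is the t-based power at 41 per arm. The normal approximation gives 80.7%.

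**4. Whether the ranked endpoint escapes.** The high and very high risk counts are the listed items that pass a blinded ranking. The ranking is protected, but the pool it works on is the same one, so these counts are protected only in part.

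**The case against.** The strongest reply is that this is a condensed article. Who codes the discrepancies, whether that person is masked and what counting rules apply are details that a full protocol may hold, and comparing drug, dose and frequency may be largely mechanical on a form not shown here. That is fair as far as silence goes. It does not reach what the article does state: the blind is attached to clinical significance, and one identification source belongs to one arm. A masked counter would still face both the extra interview and the identifiable record.

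Three stronger readings are tempting, and the article supports none of them.

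- *The count is made open-label.* No section says so. The article is silent about the counter.
- *All staff know the arm.* Patients and the intervention pharmacist do. For the coordinator and the record reviewer nothing is stated, and the allocation envelopes are opened by a third party.
- *The choice of survey mode biases the count.* Study navigation says "The survey will be completed with a study coordinator over the telephone or in person in a private clinic room, or it will be self-completed", but this describes the baseline survey of all participants, before the clinic review, and has no link to arm. Variation unrelated to arm adds noise rather than bias.

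Two further objections stand in part. The size is illustrative: at a shift of 0.31, one fifth of the design effect (0.31 / 1.56 = 0.20), rejection rises only from 5% to 8.6%. And where the pharmacist's list makes the record more accurate, a lower count is the intervention working, not bias. The concern there is that the list reveals the arm to whoever counts.

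**Conclusion.** The point holds in limited form. The article states blinding for the ranking of discrepancies and not for their identification and count, while the first hypothesis, the 41 per arm and the two raw-count comparisons rest on that count. As written, identification also uses a source available in one arm only and a record from which the arm can be inferred.

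The size cannot be fixed from the document. Assumed shifts of 0.31 to 0.62 per patient give 8.6% to about 20% rejection with no true effect, or bring power down to 60.9% to 39.1% if they oppose the planned reduction. These figures assume 41 analysed per arm, SD 2.5 in both arms and a t test on the per-patient count. Neither the size nor the direction of any shift is known. This is an inexpensive improvement to outcome assessment. It does not show that the count will be biased.

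**What to change.** For the primary count:

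1. Use the same sources in both arms, namely questionnaire recall against the medical record at baseline and at the 6-month follow-up. Keep the intervention-only reconciliation interview out of this count. What it finds can be reported with the medication-related problems, which are already assessed in the intervention arm alone.
2. Transcribe the two lists for each visit onto a standard form with arm, time point and authorship removed, and shuffle the forms.
3. Have discrepancies identified from these forms by written rules, before the risk ranking, by existing panel members who did not deliver the intervention. The last condition matters because the panel must include a clinical pharmacist and the trial evaluates a single one.

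The cost is some transcription and coding time by existing staff. No patients or visits are added and the 41 per arm is unchanged. Trial status reports that recruitment is complete, but the change acts on collected questionnaires and records and can be made before the ranking planned for study completion.
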